#### Data Analysis

Continuous data will be presented as mean ± standard deviation (SD) and we will use the Student's *t*-test or analysis of variance for comparisons between groups when the variables are normally distributed. Otherwise, we will present data as median and interquartile range and will use Wilcoxon rank-sum test for comparisons. Categorical data will be presented as percentages and χ^2^ test or Fisher's exact test will be selected for data comparison. For the study endpoints, pneumonia and MACE will be compared between the IMT group and the control group with the odds ratio (OR). Other endpoints will be compared between groups as appropriate. The SAS version 9.4 (SAS Institute, Cary, NC) will be used to perform our statistical analyses. *P* values will be 2-sided and *P* < 0.05 will be regarded as significant.

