## Abstract

**Background:** Uncommonly high rates of pneumonia in patients with acute myocardial infarction (AMI) undergoing primary percutaneous coronary intervention (PCI) have been observed during recent years. Inspiratory muscle training (IMT) could reduce pneumonia in patients undergoing coronary artery bypass grafting and other cardiac surgeries. The relationship between IMT and AMI is unknown. Here, we describe the feasibility and potential benefit of IMT in patients at high risk for pneumonia with AMI who have undergone primary PCI.

**Methods:** Our study is a prospective, randomized, controlled, single-center clinical trial. A total of 60 participants will be randomized into an IMT group and control group with 30 participants in each group. Participants in the IMT group will undergo training for 15 min *per session*, twice a day, from 12 to 24 h after primary PCI, until 30 days post-randomization; usual care will be provided for the control group. The primary endpoint is the change in inspiratory muscle strength, the secondary endpoint included feasibility, pneumonia, major adverse cardiovascular events, length of stay, pulmonary function tests measure, and quality of life.

**Discussion:** Our study is designed to evaluate the feasibility of IMT and its effectiveness in improving inspiratory muscle strength in participants with AMI who have undergone primary PCI.

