### Study Endpoints

#### Primary Endpoint

##### Change in Inspiratory Muscle Strength

Static MIP will be selected for the estimation of inspiratory muscle strength. A standard measurement according to the *ERS Statement on Respiratory Muscle Testing at Rest and during Exercise* published by the European Respiratory Society (ERS) will be taken (14) (Powerbreathe® K5). The MIP test will be performed at baseline and at 30 days post-randomization.

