### Statistical Analysis

#### Sample Size Calculation

Our sample size calculation was based on a previous study (20). The mean of the MIP difference between the experimental group and the control group was estimated to be 15 cm H_2_O, the standard deviation was 12 cm H_2_O, the significance level was α = 0.05 and the test power was 1-β = 0.8. The resulting required sample size for each group was 11. Considering our projected 20% attrition rate, the sample size of each group should be increased to 14. To better study the secondary endpoints, a total of 60 cases will be included in the final analysis.

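### The stated test for change in MIP does not adjust for baseline MIP and is settled only after a look at normality; one pre-specified ANCOVA would be a free improvement

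*Protocol article*

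**What the plan says.** The Abstract defines the endpoint: "The primary endpoint is the change in inspiratory muscle strength". The section on change in inspiratory muscle strength adds the timing: "The MIP test will be performed at baseline and at 30 days post-randomization". Each patient who completes the trial therefore has a baseline value and a day-30 value.

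The Data Analysis section gives one general rule for all continuous variables. It is Student's t-test or "analysis of variance for comparisons between groups when the variables are normally distributed"; otherwise medians and interquartile ranges are presented and the authors "will use Wilcoxon rank-sum test for comparisons". No covariate is named and no criterion for normality is given. Pneumonia and MACE are then singled out for an odds ratio. The remaining endpoints, MIP among them, are left to whatever comparison is suitable.

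The Sample Size Calculation works on the mean scale: "The mean of the MIP difference between the experimental group and the control group was estimated to be 15 cm H_2_O". Alpha is set at 0.05 and power at 80%. On spread the section says only that "the standard deviation was 12 cm H_2_O"; whether this SD belongs to the change or to the day-30 value is not stated.

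**The concern.** Two features of the stated method could be better at almost no cost.

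1. **Baseline MIP enters only by subtraction.** A change score fixes the coefficient of baseline at 1. With equal variances at both visits, the coefficient that minimises variance is the correlation r, which is below 1. The change score therefore over-corrects. It carries more variance than necessary, and if the arms differ at baseline by chance, part of that difference remains in the result with the opposite sign.
2. **The estimated quantity is not fixed.** A t-test goes with a difference in means in cm H2O, the quantity behind the planned 15. A rank-sum test goes with a shift in ranks and would be reported with medians. Which one becomes the primary result depends on the observed distribution, judged by an unstated criterion.

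At stake are the width of the primary confidence interval and whether the reported effect is sure to be the quantity the trial was sized on. The validity of the trial is not at stake.

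**Working it through.** **Inputs from the protocol article.** Difference 15 cm H2O, SD 12 cm H2O, two-sided alpha 0.05, power 0.80, 11 per group, 14 per group after 20% attrition, 60 patients in total (30 per arm). With 20% attrition, 30 × 0.8 = 24 per arm would be evaluable.

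**Assumptions, not in the article.** Equal SD s at both visits; baseline to day-30 correlation r from 0.5 to 0.9; SD 12 read as the SD of change.

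**Step 1: the plan's own figure.** n per group = 2 × (1.96 + 0.842)² × 12² / 15² = 10.05, rounded up to 11. Then 11 / 0.8 = 13.75, rounded up to 14. Both stated figures reproduce.

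**Step 2: power of the unadjusted test at the planned size.** By the noncentral t distribution it is 98.9% at 24 per arm and 99.7% at 30 per arm for 15 cm H2O.

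**Step 3: variance with and without adjustment.**
- Change score: 2s²(1 − r)
- ANCOVA: s²(1 − r²)
- Ratio: (1 + r)/2

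**Step 4: confidence interval at 24 per arm.** Half-width = t × SD × √(2/24).
- Unadjusted, 46 df: 2.013 × 12 × 0.2887 = 6.97.
- ANCOVA, 45 df (t = 2.014), SD = 12 × √((1 + r)/2):

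| r | Variance ratio | Residual SD | Half-width at 24 per arm | Detectable difference, 80% power, 30 per arm |
|---|---|---|---|---|
| change score | 1 | 12.00 | 6.97 | 8.83 |
| 0.5 | 0.75 | 10.39 | 6.04 | 7.64 |
| 0.7 | 0.85 | 11.06 | 6.43 | 8.14 |
| 0.8 | 0.90 | 11.38 | 6.62 | 8.37 |
| 0.9 | 0.95 | 11.70 | 6.80 | 8.60 |

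Widths and differences are in cm H2O. The detectable differences ignore the one degree of freedom spent on the covariate. Put as sample size, 24 per arm with ANCOVA is worth 24/0.75 = 32 per arm on the change score at r = 0.5, and 24/0.95 ≈ 25 at r = 0.9.

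**Step 5: chance imbalance, 30 per arm.** If SD of change = 12, then s = 12/√(2(1 − r)). The standard error of the baseline difference is s√(2/30), and a baseline difference b shifts the change contrast by (1 − r)b.
- r = 0.5: s = 12.0, one SE = 3.10, shift 1.55 cm H2O.
- r = 0.7: s = 15.5, one SE = 4.00, shift 1.20.
- r = 0.9: s = 26.8, one SE = 6.93, shift 0.69.

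A two-SE imbalance at r = 0.7 (8.0 cm H2O) gives 0.3 × 8.0 = 2.4. ANCOVA removes this shift.

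**Step 6: does the switch of test damage error control?** A simulation at 30 per arm used 10,000 runs, a Shapiro test in each arm, then a t-test or Wilcoxon. Type I error was 0.050 for normal data and 0.044 for log-normal data. No inflation appeared in these two cases.

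**The case against.** The best defence is that nothing here is wrong. A change score already subtracts baseline, the unadjusted comparison is unbiased over repeated randomisation, and power is about 99% on the plan's own inputs. A one-SE imbalance moves the estimate by only 0.7 to 1.5 cm H2O against 15. A two-SE imbalance is exceeded by chance in only about 5% of trials. The Data Analysis section is a general paragraph in a condensed article, and covariates are often left to a statistical analysis plan.

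Most of this stands and limits the point to an improvement. The last argument does not dispose of it. The article is not silent: it states a method and makes the choice of test conditional on the data, and that stated method can be bettered. The high power also depends on an effect and SD borrowed from an earlier study, while the Introduction says IMT has not been evaluated in AMI. If the true effect is smaller, precision counts for more.

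Stronger readings are tempting and are not supported:
- A reader might infer that the trial ignores baseline MIP. It does not; the endpoint is a change.
- A reader might compute the loss for a comparison of day-30 values alone, where the variance ratio is 1 − r² (0.75 down to 0.19 for r from 0.5 to 0.9). The endpoint definition does not describe that analysis.
- A reader might call the shift in Step 5 a bias. It is conditional on one allocation and is already reflected in the unadjusted standard error.
- A reader might suspect an inflated false-positive rate from the normality check. The simulation shows none.

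**Conclusion.** The point holds as a free improvement. The stated analysis is valid and well powered for 15 cm H2O, but it is less precise than it could be, and it does not fix in advance whether the primary result is a mean difference or a rank shift.

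The gain from baseline adjustment is 5% to 25% of the variance for r from 0.9 down to 0.5. At 24 per arm, the 95% CI half-width goes from about 7.0 to about 6.0–6.8 cm H2O. The residual effect of chance baseline imbalance is also removed.

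The variance ratios rest on equal variances at both visits and the assumed range of r. The figures in cm H2O rest also on reading SD 12 as the SD of change, which the article leaves open.

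**What to change.** State one primary analysis in the Data Analysis section: ANCOVA of day-30 MIP (or of change, which gives the same treatment estimate) on randomised arm with baseline MIP as covariate. Report the adjusted mean difference in cm H2O with its 95% CI, using a robust standard error if residuals are skewed. Use this model whatever a normality check shows, and keep the Wilcoxon rank-sum test as a sensitivity analysis only.

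The same model can serve the continuous secondary endpoints that have baseline and day-30 values, namely the spirometry measures and the SF-36 and EQ-5D scores.

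The cost is a change of wording and one degree of freedom. No new data, visits or patients are needed, and the estimate stays on the cm H2O scale used for the sample size.

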### Objectives

The aim is to assess the effectiveness of IMT by measures including the improvement of inspiratory muscle strength, pulmonary function, and quality of life, and by the avoidance of clinically adverse events. We will also assess the feasibility of IMT by examining the safety of training performance and through use of a satisfaction questionnaire.

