##### Quality of Life

Questionnaires including the 36-item short-form (SF-36) (16), Modified Medical Research Council (MMRC) dyspnoea scale (17) and EQ-5D-3L (18) will be used for the assessment of quality of life in our participants. Both interviews will be performed twice, first at baseline and again at 30 days post-randomization.

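### The analysis rules name no method for ordered grades, so MMRC dyspnoea may be tested without using the order of the grades or the baseline value (minor, secondary endpoints only)

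*Protocol article*

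**What the plan says.** The rules stand in the protocol article under Statistical Analysis, Data Analysis. Normally distributed continuous variables get a t-test or analysis of variance. For the rest of the continuous variables: "Otherwise, we will present data as median and interquartile range and will use Wilcoxon rank-sum test for comparisons". For categories: "Categorical data will be presented as percentages and χ^2^ test or Fisher's exact test will be selected for data comparison". Pneumonia and MACE are then singled out for an odds ratio, followed by: "Other endpoints will be compared between groups as appropriate". Tests are two-sided at 0.05.

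The graded outcomes appear under Secondary Endpoints, Quality of Life, where, alongside SF-36, the "Modified Medical Research Council (MMRC) dyspnoea scale (17) and EQ-5D-3L (18) will be used for the assessment of quality of life in our participants". They are measured at baseline and at 30 days. That section does not class them as continuous or categorical, and does not say whether EQ-5D-3L is analysed by dimension or as a score. The Objectives list "improvement of inspiratory muscle strength, pulmonary function, and quality of life" among the measures of effectiveness.

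**The concern.** An MMRC grade is an ordered category. Someone applying the two stated data types literally could well treat it as categorical, tabulate percentages and run χ² or Fisher's exact test. Those tests treat the grades as unordered labels. A consistent shift of patients to milder dyspnoea gets no more credit than a scatter of the same size in both directions, and the P value carries no direction. Someone else could, within the same text, use Wilcoxon and reach a different result from the same data.

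The named tests also leave the baseline grade unused, unless they are applied to a change score, and the article speaks of change as the endpoint only for inspiratory muscle strength.

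The stake is modest but real. Quality of life is part of the effectiveness claim, and the Sample Size Calculation raises the trial from 14 per group to 60 in total for the benefit of the secondary endpoints. An order-blind test gives back part of that gain.

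**Working it through.** **1. The plan's own figure.** From the Sample Size Calculation: difference 15, SD 12, two-sided α = 0.05, power 0.80.

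n per group = 2 × (1.960 + 0.842)² × 12² / 15² = 2 × 7.85 × 0.64 = 10.05, rounded up to 11. With 20% attrition, 11 / 0.8 = 13.75, rounded up to 14. Both stated figures reproduce. They concern MIP only; the article gives no target effect, grade distribution or power for MMRC or EQ-5D-3L.

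**2. Patients available.** Randomization gives 30 per arm. With the projected 20% attrition, 30 × 0.8 = 24. The range is therefore 24 to 30 per arm.

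**3. Assumptions (not in the article).** MMRC has five grades, and each EQ-5D-3L item has three levels. The effect is a common odds ratio (OR) acting on every cumulative split. With C_k the control probability of grade k or lower, the treated odds are OR × C_k / (1 − C_k). Example: control grades 40/30/15/10/5% have cumulative proportions 0.40, 0.70, 0.85, 0.95 and odds 0.667, 2.333, 5.667, 19. At OR 3 the odds become 2, 7, 17, 57, so the treated grades are 66.7/20.8/6.9/3.8/1.7%.

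**4. Tests compared.** Pearson χ² = Σ (observed − expected)² / expected, with up to 4 degrees of freedom, against the tie-corrected Wilcoxon rank-sum test. Both are two-sided at 0.05, with 20,000 simulated trials per setting (Monte Carlo standard error at most √(0.25/20,000) = 0.35 points).

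**5. Results.** In the example with 30 per arm, power is 15% (χ²) against 29% (rank) at OR 2, and 34% against 59% at OR 3. With 24 per arm at OR 3 it is 26% against 49%. In this example the rank test on 24 per arm (49%) beats χ² on 30 per arm (34%).

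Gain of the rank test over χ², in points, across four assumed five-grade distributions from even to very mild (60/25/10/4/1%):

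| OR | 30 per arm | 24 per arm |
|---|---|---|
| 1.5 | 5.3–6.1 | 4.5–5.4 |
| 2 | 12.0–14.6 | 10.8–12.5 |
| 2.5 | 17.3–21.6 | 15.0–18.8 |
| 3 | 20.4–24.6 | 18.5–23.4 |
| 4 | 21.7–25.3 | 22.9–26.7 |
| 5 | 16.5–23.7 | 21.3–25.4 |

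- With no effect, χ² rejects in 3.2–4.8% and Wilcoxon in 4.6–5.0%, so the gain is not bought with false positives.
- If only four grades are used (30/35/25/10%), the gain at 30 per arm is 4.8–19.3 points.
- Against Fisher's exact test (1,500 runs, five grades, 30 per arm) the gain is 7–14 points at OR 2 and 14–21 at OR 3.
- For a three-level item, the gain is 2.9–11.8 points at 30 per arm and 1.7–11.9 at 24.

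**6. Using the baseline grade.** Assume five grades at 30/35/20/10/5% and a latent correlation of 0.5 between baseline and day 30. A proportional-odds model adjusted for baseline grade then adds further power over Wilcoxon: about 4–7 points at OR 2 and 9–11 at OR 3 in 1,000 runs per setting, and 9–12 points in a separate set of runs. False positives stay near 5% (3–6%).

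**The case against.** The strongest objection is that no wrong test has been fixed. A reader might infer that MMRC and EQ-5D-3L are assigned to χ²/Fisher, but no section says so. Quality of life belongs to the endpoints that the article leaves open, and Wilcoxon, the test that does better in the simulation, is already named. This stands. The point is that the order-respecting choice is allowed but not required.

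A reader might also infer a loss of about 20 points. The article supplies neither a grade distribution nor a target effect, and a loss near 20 needs five well-used grades and an odds ratio of roughly 2.5 or more. At smaller effects it is well below that. Fisher's exact test, a likely choice with sparse cells, loses less than χ². EQ-5D-3L is a weak example, and drops out if scored as an index. All of this stands.

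Two further objections carry partial weight. Percentages by arm would show the direction, although the test itself would not. And a journal article condenses, so a fuller analysis plan may already settle the test for each instrument. The point therefore concerns the set of rules that the article does state, which has no class for ordered data, and not the absence of a detailed plan.

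**Conclusion.** The concern holds in a limited form. The stated rules have no class for ordered grades, the only tests named for categories ignore order, and no named two-group test uses the baseline value. Two analysts could both comply and test the same MMRC data differently.

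If the categorical rule were used for five-grade MMRC, the loss against a rank test would be roughly 5 to 25 points (up to 27 in one setting with 24 per arm). It would be about 3–12 points for a three-level EQ-5D-3L item and nil for an index score. These sizes rest on assumed grade distributions and a proportional-odds effect. The article does not support saying that the plan applies the wrong test, or that a loss of any particular size is built in. The MIP endpoint and the sample size are untouched. Severity is minor.

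**What to change.** Add one sentence to Data Analysis. Suggested text: *MMRC grade (and EQ-5D-3L dimensions, only if reported by level) will be compared at day 30 with a proportional-odds model adjusted for baseline grade and reported as a common odds ratio with 95% confidence interval; if the model does not converge, the Wilcoxon rank-sum test will be used.* Keep χ² and Fisher's exact test for binary and unordered variables, and state whether EQ-5D-3L is analysed by level or as a score.

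The change needs no new data, patients or procedures. The costs are a summary that is slightly less familiar to readers and a proportional-odds assumption; percentages by grade and arm can still be shown beside it. The fallback should depend on non-convergence alone, so that the choice of test cannot follow the result.

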##### Length of Stay (LOS)

Length of stay will be assessed by calculating the number of days the patient is in the hospital.

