## Discussion

To the best of our knowledge, the proposed protocol is the first study to assess the safety and efficacy of IMT in patients with AMI undergoing primary PCI who are at a high risk of pneumonia during the acute period. Studies have rarely focused on the uncommonly high rate of pneumonia after AMI, so the potential benefits of IMT for these patients may have been neglected. We will focus on the improvement of inspiratory muscle strength after 30 days of training. In addition, we will record the clinical adverse events and the satisfaction of these patients and try to determine whether IMT has a potential benefit for decreasing incidence of pneumonia, MACE and length of stay (LOS), and also determine if IMT could benefit pulmonary function and quality of life.

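### The plan calls any two-sided P < 0.05 significant, secondary endpoints included, although it says elsewhere that these are to be explored; the chance of at least one false benefit among them is roughly 1 in 10 to 1 in 3

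*Protocol article*

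**What the plan says.** The Abstract names one primary endpoint: "The primary endpoint is the change in inspiratory muscle strength". It then lists the others: "the secondary endpoint included feasibility, pneumonia, major adverse cardiovascular events, length of stay, pulmonary function tests measure, and quality of life".

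In Data Analysis, "pneumonia and MACE will be compared between the IMT group and the control group with the odds ratio (OR"), and the remaining endpoints are also to be compared between groups. The section ends with one rule for all of this: P "values will be 2-sided and" P < "0.05 will be regarded as significant". No endpoint is exempted, and no order of testing is given.

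Three other places bear on how secondary results will be read:

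- Objectives lists pulmonary function and quality of life beside inspiratory muscle strength as measures of effectiveness.
- Sample Size Calculation derives 14 per group for MIP and then goes further: "To better study the secondary endpoints, a total of 60 cases will be included in the final analysis".
- The Discussion says the trial will "also determine if IMT could benefit pulmonary function and quality of life". However, the same sentence speaks more cautiously of trying to find a potential benefit on pneumonia, MACE and length of stay. The limitations paragraph gives exploration of the secondary endpoints, pneumonia above all, as the reason for the larger sample.

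**The concern.** The intent is at least partly exploratory, but the decision rule does not reflect it. Read as written, an isolated P < 0.05 on one spirometry value or one questionnaire score has the same standing as a significant result on MIP. Because Objectives counts pulmonary function and quality of life as measures of effectiveness, such a result could be reported as a demonstrated benefit.

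Two features of the trial add to this. Controls receive standard care and no sham device is described, so participants will know their group, and the questionnaires are open to that knowledge. The Discussion also presents the trial as the first of its kind in these patients, so a single positive secondary result would attract attention.

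What is at stake is what the trial may claim. The primary analysis is not in question.

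**Working it through.** **The plan's own figure.** With a difference of 15, SD 12, two-sided α 0.05 and power 0.80, n = 2 × (1.960 + 0.842)² × 12² / 15² = 10.05, so 11 per group. Allowing for 20% attrition, 11 / 0.8 = 13.75, so 14 per group or 28 in all. Both stated figures reproduce. The plan states no error rate across the secondary endpoints.

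**Counting the secondary tests.**

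- Pneumonia 1, MACE 1, length of stay 1 ("Length of stay will be assessed by calculating the number of days the patient is in the hospital").
- Spirometry 4: FEV1, FVC, FEV1/FVC and VC.
- Questionnaires 3: SF-36, MMRC and EQ-5D-3L at one score each.

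That makes 10. Scoring is not stated. If SF-36 is analysed as eight domains the count is 17, and with a second EQ-5D output it is 18. Feasibility items are left out.

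**Direction.** The tests are two-sided, so under no effect a test rejects in favour of IMT with probability 0.025. For k independent tests:

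- any false positive, either direction: 1 − 0.95^k
- at least one false positive favouring IMT: 1 − 0.975^k

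**Correlation.** The spirometry values share components and questionnaire scores move together, so independence gives an upper figure. Sets of equally correlated normal test statistics were simulated, 200,000 per setting, counting sets with at least one value above 1.96.

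| Tests | Either direction, independent | Favouring IMT, independent | Favouring IMT, corr. 0.3 | corr. 0.5 | corr. 0.7 |
|---|---|---|---|---|---|
| 10 | 40.1% | 22.4% | 17.8% | 14.2% | 10.7% |
| 18 | 60.3% | 36.6% | 26.5% | 19.9% | 13.9% |
| 8 | 33.7% | 18.3% | 15.3% | 12.5% | 9.6% |
| 16 | 56.0% | 33.3% | 24.3% | 18.8% | 13.3% |

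**Why 8 and 16 are shown.** The Introduction gives pneumonia rates of 2% to 7%, which is 0.6 to 2.1 expected cases among 30. With 30 per group and no effect, Fisher's exact test at 0.05 rejects (either direction) with probability 0.003% at a 2% rate and 0.4% at 7%, so it adds almost nothing to the total. If MACE is as rare (an assumption), the effective count falls by two.

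This depends on Fisher's test being the one used. Data Analysis also allows the χ² test, whose size without continuity correction is 0.3% at a 2% rate but 4.4% at 7%. The enrolled patients are selected for high risk, so the rate may be higher. At 15%, Fisher's test still rejects only 1.7% of the time.

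**The case against.** The strongest reply has four parts.

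*This is routine wording, and control may sit in an analysis plan that is not shown.* A condensed article may indeed leave multiplicity to that plan, and the absence of an adjustment method is not the point here. But Data Analysis does state a rule, placed directly after the secondary comparisons and without exception. If a separate plan treats them differently, the published rule has to be brought into line with it.

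*The authors already present the secondary endpoints as exploratory.* This largely stands. A reader might infer from the doubled sample that secondary results are meant to be confirmatory, but the limitations paragraph explains the same enlargement as exploration, and the Discussion speaks of trying to find a potential benefit. The documents therefore do not support a charge of confirmatory intent. They support a narrower one: the rule does not match the intent.

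*The risk is easily overstated.* This also stands. A reader might take the 40% to 60% figures to mean that a false claim of benefit is likely. Those figures count apparent harm as well as benefit and assume independence. In the benefit direction it would take 28 independent tests to pass 50%, well above any count the document supports. The upper end of 18 tests also rests on a scoring assumption.

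*Unadjusted secondary endpoints below a single primary are common in small trials.* True. That argues against making an adjustment mandatory, but not against labelling the results.

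**Conclusion.** The point holds as a mismatch between the stated significance rule and the plan's own exploratory purpose. If IMT does nothing, the chance of at least one secondary result significantly favouring it is roughly 1 in 10 to 1 in 3: 22% to 37% for 10 to 18 independent tests, and about 11% to 26% at correlation 0.3 to 0.7. Dropping pneumonia and MACE as near-inert gives 18% to 33% with independence and about 10% to 24% with correlation. Against 2.5% for one test, 10.7% to 36.6% is about 4 to 15 times as high.

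The range rests on one to eight scores for SF-36, one or two for EQ-5D, and equal correlation among all endpoints. It covers chance alone; any effect of participants knowing their group would come on top.

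The type I error of the single primary endpoint is unaffected, and so is its sample size. The change is worth making because it settles what the trial may claim, but it does not threaten the main result.

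**What to change.** In Data Analysis, replace the general rule with wording such as: *The two-sided 5% significance level applies only to the between-group comparison of the change in MIP. Secondary endpoints will be reported as between-group estimates with 95% confidence intervals; these are exploratory and will not support claims of significance.* The odds ratios already planned for pneumonia and MACE fit this without change. The exploratory label is essential, because intervals read one by one for excluding no effect would recreate the same multiplicity.

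If the sponsor wants a formal claim on a few secondary endpoints, name them in advance and adjust across that short list, for example by Holm's method. Adjusting all of them is not needed. It would be severe: Bonferroni thresholds would be 0.05 / 10 = 0.005 or 0.05 / 18 = 0.0028.

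The cost is one or two sentences, with no change to sample size, data collection or conduct. The small downside is that secondary results can no longer be headlined as significant.
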